#### 2.7.4. Blood Pressure (Systolic and Diastolic)

Blood pressure of right upper limb will be measured in the sitting position at each study visit using a validated semiautomatic sphygmomanometer (Omron HEM-705CP, Dalian, China) by trained nurses. Two measurements will be conducted at interval of at least 3 min, and the average of two readings will be used for analysis. If the difference between the first two readings is ≥5 mm Hg, additional (one or two) readings will be obtained. 

Hypertension is defined as self-reported history of hypertension or systolic blood pressure (SBP) higher than 140 mmHg or diastolic blood pressure (DBP) higher than 90 mmHg [26].

#### 2.7.5. Dietary Data and Physical Activity Data

Dietary data and physical activity data will be measured at baseline, day 45 and day 90. Dietary data assessment will be based on the Food Frequency Questionnaire (FFQ), dietary logs and pictures on the app. The type, amount and frequency of food intake will be recorded by trained investigators. The amount of food will be estimated using the references of food models or photographic models [27]. Nutrients intake will be assessed using the Chinese Food Composition Table [28]. Physical activity will be assessed through the exercise logs, pictures and the average steps of 3 days before the baseline visit, day 45 and day 90 using the sports bracelet.

### 2.8. Sample Size Calculation

The sample size was calculated for a one-way analysis of variance (ANOVA) comparing the mean change in between-group (three groups) BMI from preintervention to postintervention. According to related researches, the clinically meaningful difference in change in BMI was set to 1 kg/m^2^ and the mean change in BMI of the 12-week diet and exercise group, the 12-week exercise group and the control group was −2.8, −2.5 and −0.9 kg/m^2^, respectively. The standard deviation (SD) was assumed to be equal for all three groups and was set to SD = 1.4 Kg/m^2^ [29,30]. To obtain a power of 0.90 for the overall test of differences in means, using a significance level of 0.05, 13 individuals are required in each group. To account for the three stratification groups (age: 60~66, 67~73 and 74~80), a further 26 individuals are required. Considering the study will be conducted in 5 centers, approximately 200 individuals are required for each group. To account for 20% dropout, approximately a total of 250 individuals are required for each group. Calculations were performed using PASS statistical software Version 15.0.2 (NCSS, Kaysville, UT, USA).

### 2.9. Statistical Analysis

Continuous data will be first tested for normal distribution using the Kolmogorov-Smirnov test and presented as mean ± standard deviation (SD) if normally distributed, or median [interquartile range (IQR)] if not. Categorical data will be presented as percentages.

The effect of mobile-based lifestyle intervention on BMI, parameters of glucose and lipid metabolism, body composition, C-reactive protein, liver enzymes, uric acid, copeptin, irisin, adiponectin and blood pressure among the three groups will be investigated by One-way ANOVA or Kruskal-Wallis H test. 

*p* values will be two-tailed and differences will be considered significant at *p* < 0.05. All analyses will be performed using SPSS software Version 23.0 (SPSS Inc., Chicago, IL, USA).

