## 2. Materials and Methods

### 2.1. Sample Selected

The recruitment of the study subjects will take place in communities through advertisements in five cities (Jinan, Taiyuan, Nanchang, Hefei, and Guangzhou) in China. After recruitment, basic information such as social demographics, disease history, drug use and family history will be collected.

Subjects eligible for this trial must meet the following inclusion criteria: (1) age between 60–80 years old; (2) body mass index (BMI) ≥ 24; (3) living or working in Jinan, Taiyuan, Hefei, Nanchang and Guangzhou and (4) ability to use smart phones. The exclusion criteria will include: (1) participation in any activities related to weight management; (2) diagnosed with psychiatric disorder such as cognitive dysfunction, schizophrenia or depression; (3) with pacemakers or other medical electronic devices; (4) with walking disability; (5) history of surgical treatment of obesity; (6) excessive drinking and (7) unwillingness to change their habits. 

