## Figures and Tables

**Figure 1 ijerph-18-04854-f001:**
[figure not shown]
The flow diagram of this trial.

**Table 2 ijerph-18-04854-t002:** Primary and secondary outcomes.

Outcomes	Assessments
Primary outcome	the between-group (three groups) difference in body mass index at the end of intervention
Secondary outcomes	parameters of glucose and lipid metabolism, CRP, liver enzymes, uric acid, copeptin, irisin, adiponectin, body composition, blood pressure, dietary data and physical activity data

CRP: C-reactive protein.

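### The primary BMI test is left as ANOVA or Kruskal-Wallis, with a normality test on the trial data as the only criterion in sight; one mean-based model should be named in advance

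*Protocol article*

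**What the plan says.** The primary outcome in Table 2 is "the between-group (three groups) difference in body mass index at the end of intervention". Section 2.9 handles it in two steps that are not joined.

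- Descriptive step: "Continuous data will be first tested for normal distribution using the Kolmogorov-Smirnov test", and the data are then "presented as mean ± standard deviation (SD) if normally distributed, or median [interquartile range (IQR)] if not".
- Inferential step, in a separate paragraph: the effect of the intervention on BMI and a list of other outcomes "among the three groups will be investigated by One-way ANOVA or Kruskal-Wallis H test". This sentence gives no criterion for choosing between the two tests. The significance level is 0.05, two-sided.

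Section 2.8 is written for one of the two tests only: "The sample size was calculated for a one-way analysis of variance (ANOVA) comparing the mean change in between-group (three groups) BMI". It takes 1 kg/m2 as the difference in change that matters clinically, and plans about 200 evaluable participants per group (250 before dropout). Section 2.1 requires "body mass index (BMI) ≥ 24" and sets no upper limit. The Discussion (section 4) promises that age, sex and other factors will enter the analyses as covariates.

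**The concern.** For the primary outcome, the choice between a test of means and a test of ranks is open. Either the normality result selects the test, so that the trial data pick the primary analysis, or nothing selects it and the choice can be made after the data are seen. On neither reading is the primary test fixed.

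The two branches do not answer the same question. Section 2.8 reasons in mean change and a 1 kg/m2 benchmark. Kruskal-Wallis compares ranks. In that branch section 2.9 would also replace means and SDs by medians and IQRs. A reader would then have a rank p-value and three medians, and no mean difference to compare with the benchmark.

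The trigger is plausible. A lower cut at BMI 24 tends to leave a right-skewed distribution, and at about 200 per group a normality test can detect modest skew. That is also the sample size at which ANOVA least needs normal data.

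**Working it through.** **Step 1: the plan's own figure.** Inputs from section 2.8: mean changes −2.8, −2.5 and −0.9 kg/m2, common SD 1.4, alpha 0.05, power 0.90.

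- Grand mean = −6.2/3 = −2.067. Squared deviations are 0.538, 0.188 and 1.361, which sum to 2.087.
- Noncentrality λ = n × 2.087/1.4² = 1.065n. Power comes from the noncentral F with 2 and 3(n − 1) degrees of freedom.
- n = 12 gives 0.873 and n = 13 gives 0.901, so the stated 13 per group is reproduced.
- 13 × 3 age strata = 39; 39 × 5 centres = 195, or about 200; 200/0.80 = 250.

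The base calculation is thus a test of means. At 200 per group its power exceeds 0.999 for these means. It also exceeds 0.999 when the largest difference is 1 kg/m2 (means −0.5, 0, 0.5), for which 51 per group would give 90%.

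**Step 2: how often the normality test would reject at 200 per group.** The documents give no BMI distribution, so these shapes are assumptions. Day-90 BMI is a normal baseline (mean 24 to 27, SD 2.5 to 3.5) cut at 24, plus a normal change with SD 1.4; the resulting skew is about 0.3 to 0.6. Each case had 600 simulated trials, so the Monte Carlo standard error is at most √(0.25/600) = 0.02. Any arm means rejection at 0.05 in at least one of the three arms. Pooled means one test on 600 values, simulated without mean differences between arms. Lilliefors is the Kolmogorov-Smirnov test corrected for an estimated mean and SD.

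| Variable tested | Lilliefors, any arm | Uncorrected, any arm | Lilliefors, pooled | Uncorrected, pooled |
|---|---|---|---|---|
| Change, exactly normal | 15% | 0% | 3% | 0% |
| Day-90 BMI, baseline cut at 24 | 47–96% | 1–17% | 40–96% | 2–56% |
| Change, mildly non-normal (skew 0.5, or t with 5 df) | 82–89% | 6–20% | 83–94% | 20–41% |
| Change, skew 1 | 100% | 74% | 100% | 99% |

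The 15% in the first row is what three independent 5% tests give by chance: 1 − 0.95³ = 14%. For day-90 BMI with only 13 per group, the Lilliefors any-arm rate is 13–23%. The test therefore fires more often as the sample grows.

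**Step 3: does the switch change error rates?** One day-90 scenario was used: baseline mean 25, SD 3, cut at 24; change SD 1.4; 200 per group; Lilliefors in any arm as the selector; 3,000 trials.

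| | ANOVA always | Kruskal-Wallis always | Two-stage rule | Switched to ranks |
|---|---|---|---|---|
| No effect | 0.051 | 0.053 | 0.054 | 86% |
| Smaller effect (−1.4, −1.3, −0.9) | 0.477 | 0.476 | 0.478 | 85% |

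The Monte Carlo standard errors are √(0.05 × 0.95/3000) = 0.004 for the first row and about 0.009 for the second, so the columns cannot be told apart. With the plan's own mean changes, all three procedures rejected in every one of 500 trials.

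**The case against.** The strongest reply is that the text does not say what a reader might infer from it, and that no inferential harm is shown.

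- A reader might take the Kolmogorov-Smirnov test to be the plan's stated rule for choosing the test. It is not: section 2.9 attaches it to how data are summarised and gives the tests no criterion. This stands. The link is implied, though no other criterion appears in the document.
- A reader might conclude that the primary test will often be a rank test. The documents do not support a frequency. It depends on a BMI distribution they do not give and on choices they do not state. With normal change scores and an uncorrected test the switch would almost never occur.
- A reader might suspect an inflated type I error or lost power. Step 3 shows neither.
- The contrast between branches can be overdrawn. An overall ANOVA p-value gives no pairwise difference either, and the rank branch would still show medians in kg/m2. This stands in part: medians do not estimate the mean difference used in section 2.8, whereas a mean-based model yields that difference directly.
- Effect estimates and confidence intervals are commonly left to the analysis plan, which is not shown, and their absence is not the point here. What the article does state about the primary test is an either/or, and that is the defect.
- The simulations cover BMI only. They say nothing about the laboratory outcomes on the same list.

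**Conclusion.** The point holds in a limited form. Section 2.9 does not fix the primary test for BMI, and the only candidate selector is a normality test on the trial data. Under assumed BMI distributions cut at 24 and 200 per group, the chance of ending with a rank test runs from near 0% to above 90%, depending on details the plan leaves open. For BMI the switch is unnecessary: ANOVA held its 5% level in the scenario checked, and power was the same to within simulation error.

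The harm is to pre-specification and to the reported effect, not to error rates. The rank branch has no mean difference to set against the 1 kg/m2 and the ANOVA on means in section 2.8. This is a cheap improvement and does not threaten the trial's validity. The size of the switching range rests on the assumed BMI shapes; the unfixed choice and the mismatch with section 2.8 do not.

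**What to change.** In section 2.9, state that BMI will be analysed with one mean-based linear model whatever the normality test shows, and that between-group mean differences in kg/m2 will be reported with 95% CIs. ANCOVA with baseline BMI is a natural choice. The group difference it gives is the same whether day-90 BMI or change is the outcome, which settles one of the open choices. It can also carry covariates, which the Discussion promises and neither named test can take. Keep Kruskal-Wallis for BMI as a sensitivity analysis only, and confine the Kolmogorov-Smirnov test to the descriptive role the text already gives it.

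The cost is a sentence or two, with no extra data or participants. The base sample size is unchanged: 13 per group still gives power 0.901 for the test of mean change. The downside is that a rank test is no longer the primary fallback if BMI proves markedly skewed; the sensitivity analysis covers that case.

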## Abstract

*Background*: Promotion of a healthy lifestyle is considered a good strategy for dealing with chronic diseases. Mobile-based lifestyle interventions have shown beneficial effects in the control and treatment of chronic diseases such as diabetes, obesity and metabolic syndrome. Current clinical trials for mobile-based lifestyle intervention were mainly conducted among non-elderly populations, thus well-designed trials performed among the elderly who are more susceptible to chronic diseases are needed. The study aims to assess the effect of the mobile-based lifestyle intervention on the improvement of body weight, glucose and lipid metabolism among overweight and obese elderly adults in China. *Materials and Methods*: Participants aged 60–80 years who are overweight or obese will be randomly assigned to receive mobile-based nutrition and exercise intervention, mobile-based exercise intervention and no intervention for 3 months. Before the intervention, participants will receive the training of the mobile application and sports bracelet. The primary outcome will be the between-group (three groups) difference in body mass index at the end of intervention. The secondary outcomes will include body composition, parameters of glucose and lipid metabolism, blood pressure, dietary data and physical activity data. All these outcomes will be assessed at baseline, day 45 and day 90. *Ethics and dissemination*: The trial has been approved by the Ethics Committee of Peking University Health Science Center (IRB00001052-18039).

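### The primary outcome is BMI at the end of intervention, but the trial is sized on change in BMI and the named tests do not use baseline BMI: precision is lost, though not the power for the planned means

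*Protocol article*

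**What the plan says.** - **Primary outcome.** The Abstract states: "The primary outcome will be the between-group (three groups) difference in body mass index at the end of intervention". Table 2 repeats it. This is the BMI attained at day 90.
- **Sample size (Section 2.8).** The calculation is for a one-way ANOVA "comparing the mean change in between-group (three groups) BMI from preintervention to postintervention", with a common SD of 1.4 kg/m². The target is also on the change scale: "the clinically meaningful difference in change in BMI was set to 1 kg/m^2". The count rises from 13 per group to about 200 evaluable and 250 enrolled.
- **Analysis (Section 2.9).** BMI and the other outcomes "among the three groups will be investigated by One-way ANOVA or Kruskal-Wallis H test". The section does not say whether BMI means the attained value or the change, and it names no covariate.
- **Discussion (Section 4).** A list of possible confounders, from age and sex to living conditions and social support, is to enter the statistical analyses as covariates. Baseline BMI and centre are not on the list.

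**The concern.** The article gives two primary variables. Under randomisation the expected difference between groups is the same for attained BMI as for change, so the 1 kg/m² target carries over. The variance does not carry over. Attained BMI includes the stable differences between people, which subtraction of baseline, or adjustment for it, largely removes. An SD of 1.4 describes change and should not be expected to hold for day-90 BMI.

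If Section 2.9 is read with Table 2, the primary comparison makes no use of baseline BMI and each participant yields less information than Section 2.8 assumed. If it is read with Section 2.8, the planned SD applies but the outcome tested is not the one in Table 2. The Discussion does not settle the matter: one-way ANOVA and Kruskal-Wallis take no covariates, and the covariate that would recover the planned precision is absent from the list. At stake are the width of the confidence intervals, the power for the stated meaningful difference, and a primary result that can be read in more than one way.

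**Working it through.** **Inputs.** From Section 2.8: mean changes for A, B and C ("the control group was −2.8, −2.5 and −0.9 kg/m^2^, respectively"), SD 1.4, alpha 0.05, power 0.90, about 200 evaluable per group, meaningful difference 1 kg/m². The SD of attained BMI is not given; I assume 2.5, 3.0 and 3.5 kg/m².

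**Step 1: reproduce the plan's figure.** Power comes from the noncentral F with 2 and 3(n−1) degrees of freedom and λ = n·Σ(μᵢ − μ̄)²/SD².
- μ̄ = −6.2/3 = −2.067, and Σ(μᵢ − μ̄)² = 0.538 + 0.188 + 1.361 = 2.087.
- At n = 13, λ = 13 × 2.087/1.96 = 13.84 and power is 0.901. At n = 12 it is 0.873. The 13 per group is correct for change in BMI.
- 13 + 26 = 39; 39 × 5 = 195, stated as about 200; 200/0.80 = 250.

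**Step 2: precision at 200 per group.** The variance ratio is (SD/1.4)². The standard error of a pairwise difference is SD·√(2/200) = SD/10. For baseline adjustment, assume equal SDs at both times. Then 1.4² = 2·SD²(1 − ρ), so ρ = 1 − 1.96/(2·SD²), and the ANCOVA residual SD is SD·√(1 − ρ²).

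| Assumed SD of attained BMI | 2.5 | 3.0 | 3.5 |
|---|---|---|---|
| Variance relative to plan | 3.19 | 4.59 | 6.25 |
| SE of a pairwise difference, no baseline | 0.25 | 0.30 | 0.35 |
| Implied ρ | 0.843 | 0.891 | 0.920 |
| ANCOVA residual SD | 1.344 | 1.361 | 1.372 |
| SE with baseline BMI | 0.134 | 0.136 | 0.137 |

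Analysing change gives 1.4/10 = 0.14, about the same as ANCOVA.

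**Step 3: overall power at 200 per group, attained BMI without baseline.**

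| Means (A/B/C) | Σ(μᵢ − μ̄)² | λ at SD 2.5 / 3.0 / 3.5 | Power |
|---|---|---|---|
| Planned −2.8/−2.5/−0.9 | 2.087 | 66.8 / 46.4 / 34.1 | >0.999 in all three |
| −1/−1/0 | 0.667 | 21.3 / 14.8 / 10.9 | 0.99 / 0.94 / 0.85 |
| −1/−0.5/0 | 0.500 | 16.0 / 11.1 / 8.2 | 0.96 / 0.85 / 0.72 |

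At SD 1.4 all three patterns exceed 0.999 (for the last, λ = 100/1.96 = 51.0).

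**Step 4: where 90% is lost.** At 200 per group, overall power stays at or above 0.90 up to an SD of about 5.7 for the planned means, 3.2 for −1/−1/0 and 2.8 for −1/−0.5/0.

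**The case against.** The strongest reply is that the enrolment target makes the mismatch harmless. About 200 evaluable per group is some 15 times the formal 13. Even without baseline, the standard error of 0.25 to 0.35 is below the 1.4 × √(2/13) = 0.55 implied by the formal calculation. This stands for the planned means. It does not stand for a 1 kg/m² spread if the SD of attained BMI exceeds about 2.8 to 3.2. That SD is my assumption, and the entry floor of BMI 24 narrows the distribution, so 3.5 is best read as an unfavourable bound.

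A second reply is that a condensed article may leave the model to a statistical analysis plan. That covers the choice of extra covariates such as centre. It does not cover two different primary variables, or named tests that cannot do what the Discussion promises.

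A reader might infer more than the document supports:
- **That the primary test is underpowered.** This follows only if power for attained BMI is evaluated at 13 per group, which is not the size of the trial.
- **That the trial fails on Group A versus Group B.** The planned means differ by 0.3 kg/m² there, but Section 2.8 powers the overall test and sets 1 kg/m² as meaningful. The 0.3 was never a power target.
- **That a normality pre-test decides the primary test.** Section 2.9 says "Continuous data will be first tested for normal distribution using the Kolmogorov-Smirnov test", but ties this explicitly only to how data are presented. Using it to choose between ANOVA and Kruskal-Wallis is a plausible reading, not stated text. What remains is that no rule for the choice is given, and that Kruskal-Wallis yields no difference in kg/m² to set against the 1 kg/m² target.
- **That the plan is wholly unadjusted, or biased.** The Discussion intends adjustment, so the defect is a conflict between sections. With randomisation an unadjusted comparison is unbiased; chance baseline imbalance is already in its standard error.

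**Conclusion.** The point holds as an inconsistency with a cost in precision, and it should be fixed. The Abstract and Table 2 name attained BMI, Section 2.8 is built on change, and Section 2.9 names tests that use no baseline BMI and cannot carry the Discussion's covariates. These contradictions do not depend on any assumed figure.

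The size does. With an attained-BMI SD of 2.5 to 3.5 and equal SDs at baseline and day 90, omitting baseline makes the standard error of a pairwise difference roughly 1.9 to 2.6 times what adjustment would give (0.25/0.134 to 0.35/0.137). The power consequence is confined to effects near the stated meaningful difference. The scenario on which the trial was planned remains safe.

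**What to change.** 1. Use one primary variable in the Abstract, Section 2.8, Section 2.9 and Table 2. Day-90 BMI adjusted for baseline BMI is the natural choice; the SD of 1.4 for change is then a slightly conservative stand-in for the residual SD (1.34 to 1.37 under the assumptions above).
2. In Section 2.9, make the primary analysis an ANCOVA of day-90 BMI on group with baseline BMI, plus centre and age stratum. Table 1 schedules anthropometry at enrolment and again on day 0, so state which value is the baseline.
3. Report the A−C, B−C and A−B differences in kg/m² with 95% confidence intervals.
4. Keep Kruskal-Wallis only as a sensitivity analysis.
5. Reconcile Section 2.9 with the Discussion: say which listed covariates enter the primary model, and use their baseline values, since food intake and physical activity are also measured during the intervention.

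The cost is wording. Weight, height, age and city are already collected, the sample size need not change, and SPSS fits the model.

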Advances in mobile technology make it possible to supply health management support to patients which is both convenient and cost-effective [12]. Mobile applications (apps) for health management have been shown to play a positive role in improving several chronic diseases and may bring enormous social and economic benefits. Kumar et al. found that mobile-based lifestyle intervention could decrease the hemoglobin A1c level of Type 2 diabetes patients significantly [14]. An American study conducted among patients with obesity, hypertension, diabetes and hyperlipidemia showed that mobile-based interventions produced larger weight loss compared with the control group during the whole 12-month follow-up [15]. Another study demonstrated that overweight and obesity Korean patients, after following a mobile-based lifestyle intervention, had a clinically significant weight loss and maintained this effect during the 52-week follow-up and also showed significant improvement in metabolic syndrome parameters such as fasting glucose levels and blood lipids [16]. 

The overweight and obese elderly populations with two risk factors, aging and high-BMI, are more susceptible to chronic diseases. However, most clinical trials for mobile-based lifestyle intervention were conducted among non-elderly populations [14,15,16,17]. Considering the data on the effect of mobile-based lifestyle intervention on the control of chronic diseases among the elderly population was very limited, well-designed randomized controlled trials (RCTs) performed in the elderly are needed. 

The purposes of this study are, first, to assess the effect of the mobile-based lifestyle intervention on the improvement of body weight, glucose and lipid metabolism among overweight and obese elderly adults in China. In addition, to explore whether the mobile-based lifestyle intervention may have an effect on blood pressure, body composition, C-reactive protein, liver enzymes, uric acid and the factors associated with blood glucose or lipid including copeptin, irisin and adiponectin. Third, to compare differences between males and females. Finally, to provide suggestions for the intelligent health management among the elderly in China.

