#### 2.7.3. Parameters of Glucose and Lipid Metabolism, C-Reactive Protein, Liver Enzymes, Uric Acid, Copeptin, Irisin and Adiponectin

These parameters will be obtained at baseline, day 45 and day 90. Serum lipids [triglyceride (TG), total cholesterol (TC), high-density lipoprotein cholesterol (HDL-C), low-density lipoprotein cholesterol (LDL-C) (mg/dL)], fasting plasma glucose (FPG), hemoglobin A1C, serum uric acid, copeptin, irisin, adiponectin, insulin and C-reactive protein will be measured after an overnight fast and 2 h postprandial plasma glucose (2 hPPG) will be measured 2 h after the breakfasts at the baseline visit, day 45 and day 90 in all participants. Plasma glucose will be measured by hexokinase method. Serum TC, HDL-C and LDL-C will be measured using an enzymatic colorimetry method. Serum TG and uric acid concentrations will be determined by colorimetric. Serum ALT and AST will be measured using International Federation of Clinical Chemistry method. Serum copeptin, irisin and adiponectin will be measured with enzyme-linked immunosorbent assay. Blood hemoglobin A1C will be measured using high performance liquid chromatography. Serum insulin will be measured using chemiluminescent immunoassay and C-reactive protein will be determined by immunoturbidimetry.

Dyslipidemia will be defined as self-reported history of dyslipidemia or levels of TC ≥ 6.2 mmol/L, LDL-C ≥ 4.1 mmol/L, TG ≥ 2.3 mmol/L, or HDL-C less than 1.0 mmol/L [23]. Impaired FPG (IFG) will be defined as 6.1 ≤ FPG < 7.0 and 2 hPPG < 7.8, and IGT will be defined as FPG < 7.0 and 7.8 ≤ 2 hPPG < 11.1. Diabetes will be defined as self-reported history of diabetes or FPG ≥ 7.0 mmol/L or 2 h plasma glucose ≥ 11.1 mmol/L on 75 g oral glucose tolerance test [24]. Elevation of serum uric acid will be defined as serum uric acid level > 420 μ-mol/L after consumption of a normal daily diet [25]. 

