### 2.11. Providing Suggestions

Suggestions for intelligent health management among the elderly in China will be provided. As the elderly have their own physical and mental characteristics and knowledge structure, recommendations on how to improve compliance, how to make the health management app more friendly, how to improve ease of use, how to create incentives, how to make the health knowledge and healthy lifestyle more acceptable to the elderly will be made based on the experiences during the conduction of the study. And if the result proves to be that the mobile-based lifestyle intervention is beneficial, it would provide a successful approach for the improvement of bodyweight, glucose and lipid metabolism and a scientific evidence for intelligent health management among the elderly in China.

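### Eight glucose and lipid measures are each tested at p < 0.05 without ordering or adjustment, although their improvement is a headline conclusion

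*Protocol article*

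**What the plan says.** Table 2 of the protocol article names one primary outcome, the three-group difference in BMI at the end of intervention, and puts everything else in a single unranked secondary list.

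Section 2.9 names the outcomes to be tested: "The effect of mobile-based lifestyle intervention on BMI, parameters of glucose and lipid metabolism, body composition, C-reactive protein, liver enzymes, uric acid", and then copeptin, irisin, adiponectin and blood pressure. Differences "among the three groups will be investigated by One-way ANOVA or Kruskal-Wallis H test". One threshold covers them all: p "values will be two-tailed and differences will be considered significant at" p < 0.05.

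Section 2.7.3 shows what the glucose and lipid parameters are. The lipids are triglyceride, "total cholesterol (TC), high-density lipoprotein cholesterol (HDL-C), low-density lipoprotein cholesterol (LDL-C"). The glucose measures come from "fasting plasma glucose (FPG), hemoglobin A1C, serum uric acid, copeptin, irisin, adiponectin, insulin and C-reactive protein will be measured after an overnight fast", plus the 2 h postprandial glucose.

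The Introduction gives the purposes in order: "first, to assess the effect of the mobile-based lifestyle intervention on the improvement of body weight, glucose and lipid metabolism". Blood pressure, body composition, CRP, liver enzymes, uric acid, copeptin, irisin and adiponectin come under a second purpose, which is worded as exploration. Section 2.11 says that if the intervention proves beneficial, "it would provide a successful approach for the improvement of bodyweight, glucose and lipid metabolism and a scientific evidence for intelligent health management". The Abstract and section 5 pair body weight with glucose and lipid metabolism in the same way.

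**The concern.** The status of the glucose and lipid outcomes does not match the rule used to judge them. By design they are secondary. By stated purpose and planned conclusion they stand level with body weight. Improvement in glucose and lipid metabolism is a claim about a group of measures, and the article does not say what would establish it. Section 2.9 gives each of the eight measures its own 5% test, so the error rate of the group claim is not 5%.

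At stake is how a partly positive result would be reported. If one of the eight markers reached p < 0.05 and the other seven did not, section 2.9 would let it be called significant, and nothing in the article would stop it being reported as support for the metabolic half of the conclusion.

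**Working it through.** **The plan's own figure.** The article gives no error rate for a group of tests. Its only computed design figure is the sample size in section 2.8, which also supplies the alpha of 0.05. With mean BMI changes of −2.8, −2.5 and −0.9 and an SD of 1.4, the grand mean is −2.067 and the sum of squared deviations is 2.087. The noncentrality for n per group is n × 2.087 / 1.96. The noncentral F distribution then gives power 0.873 at n = 12 and 0.901 at n = 13. The stated 13 per group for 90% power is reproduced, as is 200 / 0.80 = 250 for dropout.

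**Counting the tests.** From section 2.7.3:
- lipids: TG, TC, HDL-C, LDL-C = 4
- glucose: FPG, 2 hPPG, HbA1c, insulin = 4
- total = 8 (7 if insulin is not counted as a glucose measure)

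The other tested secondaries are four body composition measures, CRP, ALT, AST, uric acid, copeptin, irisin, adiponectin, SBP and DBP, which makes 13. These are the measures the Introduction describes as exploratory, so they are left out of the headline calculation.

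**Chance of at least one false positive, independent tests.** With k tests at 0.05 and no true effect on any:
- 1 − 0.95^k
- k = 8: 1 − 0.95^8 = 0.337; expected false positives 8 × 0.05 = 0.40
- k = 7: 1 − 0.95^7 = 0.302

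**Allowing for correlation.** The markers are correlated, but the article gives no correlations, so these are assumed. Each three-group test is represented by its large-sample chi-square with 2 degrees of freedom, and all pairs of measures share one correlation. Simulation for the eight tests at one visit gives:

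| Assumed correlation | Chance of at least one p < 0.05 | Multiple of 0.05 |
|---|---|---|
| 0 (independent) | 34% | 6.7 |
| 0.3 | 30% | 6.1 |
| 0.5 | 26% | 5.1 |
| 0.8 | 16% | 3.3 |
| 0.9 | 12% | 2.4 |

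Each entry counts one overall three-group test per measure.

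**Effect of adjustment.** The strictest Holm step over eight tests is 0.05 / 8 = 0.00625. Under independence the chance of any false positive becomes 1 − (1 − 0.00625)^8 = 0.049, and positive correlation lowers it.

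**What adjustment costs.** With 200 completers per group, the effect detectable with 90% power by one overall test rises from Cohen's f = 0.146 at 0.05 to f = 0.178 at 0.00625. If one arm differs from two equal arms by d SDs, f = d√2 / 3, so d rises from about 0.31 to 0.38. Under section 2.8's own means and SD, the overall BMI test with 200 per group has power near 1.0, so gating on it would cost almost nothing if those assumptions hold.

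**The case against.** **A missing adjustment may be in an unseen document.** This is a condensed article, and handling of secondary multiplicity is commonly left to the analysis plan. That stands as far as it goes: a missing adjustment alone would be no finding. But section 2.9 does more than stay silent. It states the threshold and applies it to the listed outcomes, and the article itself promotes eight of them into its main conclusion. It is the pairing that needs correcting.

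**The article does not say that one marker is enough.** Correct. Section 2.11 is conditional on the intervention proving beneficial and does not define that by any single marker. A reader might infer that one positive marker with a null BMI result would trigger the conclusion. The documents do not say so; they simply do not exclude it.

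**Stronger readings a reader might draw, and why they fail:**
- *All 21 secondaries lack any exploratory status.* The Introduction uses exploratory wording for exactly the other 13. What remains is that section 2.9 and Table 2 do not carry that distinction through.
- *A chance positive is likely.* For the eight markers the figure is below one half even under independence. It exceeds one half at day 90 only if the 13 exploratory measures are pooled in and correlation is weak or absent (66% for 21 independent tests, 56% at 0.3, 44% at 0.5).
- *Two visits double the tests.* Section 2.7.3 says of the blood measures: "These parameters will be obtained at baseline, day 45 and day 90". That is a measurement schedule; section 2.9 does not say that day 45 is tested separately.
- *The trial's type I error is inflated.* BMI is a single primary outcome with one overall test at 0.05, and the secondary tests do not change its error rate.

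**Conclusion.** The point holds for the eight glucose and lipid measures at day 90. Under the rule in section 2.9, a claim resting on any one of them carries a false positive chance of about one in four at an assumed correlation of 0.5, within a range of 12% (correlation 0.9) to 34% (independence), against the nominal 5%. The size depends on the assumed correlations and on there being no true effect on any of the eight; the direction does not, because every correlation examined gives more than twice 5%. Dropping insulin from the group changes little (30% rather than 34% under independence).

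This is a worthwhile, inexpensive improvement to a secondary claim. It is not a flaw in the primary analysis.

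**What to change.** In section 2.9:
- State that the eight named glucose and lipid measures are tested at day 90 only if the overall three-group BMI test is significant at 0.05, with Holm adjustment over the eight (smallest p against 0.00625). The gate should name the overall test, since that is the BMI test the article specifies.
- Carry the Introduction's exploratory status for the other 13 measures into this section, and extend it to any day-45 results: estimates with 95% confidence intervals and no significance claim.

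In sections 2.11 and 5, limit the glucose and lipid conclusion to the markers that pass this rule.

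If the sponsor prefers no adjustment, an acceptable alternative is to label all secondary p values exploratory and limit the glucose and lipid conclusion to match.

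The cost is wording only, with no extra participants or data. The downside is that fewer secondary results can be called significant. If the true BMI effect is much smaller than section 2.8 assumes, the gate may also close off the metabolic tests.
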